#### Research team undertaking screening and data extraction

Members of the direct emergency department care team at each NHS trust will undertake the screening of electronic records for patients admitted following head injury and data extraction from case notes. Staff undertaking data extraction will undergo data extraction training, and this includes training in abbreviated injury scale coding of injuries on CT brain scans by the Trauma Audit and Research Network (TARN) which is an Association for the Advancement of Automotive Medicine-accredited trainer to ensure the use of AIS dictionary in a reliable and reproducible fashion. Data extraction will be piloted over a 1-month period. Hypothetical and non-identifiable training samples of potential patient records will be generated at both sites during the training period and will be used to check the quality of, and validate, data extraction in the research team. The research team will not be blinded to outcomes. However, most prognostic variables being collected are demographic and other factors not subject to interpretation. Patients are also not being allocated to treatment groups, and therefore, data collection is less likely to be biased in favour of a specific outcome.

### Sample size

Sample size of a prognostic study is informed by three factors: anticipated prevalence of the outcome (in this study clinical deterioration), desired sensitivity of the model to the outcome and the precision of the 95% confidence interval around the sensitivity of the model [12].

We have based our sample size on a 10% estimated prevalence of clinical deterioration in our systematic review and our desired precision of the sensitivity of the derived model for this outcome [9]. Research into discharge decision making in patients presenting to the ED with chest pain indicated that a 1/100 risk of a patient being discharged who subsequently had a significant cardiac event may be an acceptable risk threshold to both patients and clinicians [21]. Therefore, we will aim for 99% sensitivity for clinical deterioration as this may correspond to a clinically acceptable level of model accuracy.

A sample size of approximately 2000 patients is required, based upon the desired 99% sensitivity in order that the maximum marginal error of the estimate does not exceed 1.4% with a 95% confidence interval [22]. Based upon previous data collection, we estimate at least 100 patients will be eligible for inclusion per year at each site of data collection over the 10-year period of interest [23].

### Statistical analysis

#### Outcome estimate

The proportion of patients that fulfil the composite measure of deterioration will be estimated. A sample size of 2000 patients will allow us to estimate the prevalence of clinically significant deterioration with a 1.3% margin of error at a 95% confidence level.

#### Missing data

As data are to be extracted from clinical records, missing variable data will inevitably occur. Although it is possible to verify the data to judge whether missing data are missing completely at random (MAR) or associated with observed variables, it is generally impossible to prove that data are indeed MAR or whether they are not missing at random (MNAR) [24]. Multiple imputation will be used to impute missing data with the number of imputations determined by the amount of missing data, under a missing random assumption, so as to avoid excluding patients from the analysis. This will be completed using STATA with the exact method determined by the amount, type and distribution of the missing data, and we will adhere to recognised guidelines for appropriate use and reporting of methods to deal with missing data [28, 29]. After imputation, a sensitivity analysis will be undertaken to determine how the substantive results depend on the multiple imputation method employed. This is consistent with the TRIPOD recommendations with the handling of missing data in prognostic studies [12].

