### Candidate prognostic factors

Potential candidate factors have been selected a priori by identification of factors that individually predict deterioration in the study population in our systematic review, inclusion of additional factors that predict adverse outcomes in prognostic models for patients with more severe TBI and trauma and inclusion of factors that represent NICE guideline standards and criteria for treatment and investigation of head injury and TBI [1, 9, 13–15]. All factors being considered for inclusion in the final model are presented in Table 1 with the reason for their inclusion.

**Table 1 Tab1:** Prognostic factors being investigated

Factors from systematic review	Type of data	Factors from NICE guidelines	Type of data	Factors from TARN TBI/trauma model	Type of data
Age	Continuous	1st neurological examination in ED	Categorical	Admission Hb	Continuous
Sex	Categorical	Equal pupils 1st examination	Categorical	Admission platelets	Continuous
Pre-injury anti-coagulant use	Categorical	Both pupils reactive 1st examination	Categorical	Charlson Trauma Modified Comorbidity Index	Continuous
Pre-injury anti-platelet use	Categorical	SIGN of skull fracture 1st examination	Categorical	Admission BM	Continuous
GCS on arrival to ED	Categorical	Seizures in ED	Categorical	Frailty score	Continuous
BP on arrival ED	Continuous	Vomiting in ED	Categorical		
HAIS	Continuous	An occupant ejected from a motor vehicle	Categorical		
Marshall Classification	Categorical	Mechanism of injury	Categorical		
Single injury	Categorical	Amnesia	Categorical		
Comment on midline shift	Categorical	Intoxicated EToH time of injury	Categorical		
Comment on size of bleed		Seizures before arrival ED	Categorical		
Additional injuries	Categorical	Vomiting before arrival ED	Categorical		
Sats on arrival ED	Continuous	A pedestrian or cyclist struck by a motor vehicle	Categorical		
		A fall from height of > 1 m or 5 stairs	Categorical		

Comorbidities will be measured using a trauma-modified Charlson Comorbidity Index. Brain injury severity, as shown on CT scan, will be stratified using the Marshall Classification, which will be calculated from Abbreviated Injury Severity (AIS) codes for TBI using the method described by Lesko et al. [16, 17] The Charlson Comorbidity Index, AIS and Marshall Classification are internationally validated prognostic scoring systems [18, 19]. Frailty will be assessed using the clinical frailty scale described by Rockwood et al. [20].

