#### Sensitivity analysis

The 10-year period of data collection represents a long time period over which clinical practice and outcomes may have changed. To assess for this, we will estimate the yearly prevalence of clinical deterioration and note any statistically significant changes in outcome over time. In addition, because NICE guidelines were updated in 2014 (with minor changes to the indications for CT brain imaging), the prognostic model will be estimated solely for the time period 2014–2017 and compared to the model estimated for the whole time period [1].

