### Limitations

Data collection is retrospective and will be limited by the nature and accuracy of the data clinically recorded. However, such data are likely to be applicable and implementable in current routine practice. Given the large sample size required for this study and the challenges of prospectively recruiting patients in the ED, a retrospective method for data collection represents a feasible and pragmatic data collection strategy.

Outcomes will only be assessed during hospital admission and re-attendances to the hospitals where data collection is occuring. This may underestimate deterioration following discharge especially if patients die in the community or deteriorate and are readmitted to a different hospital. We will estimate the effect of this possible bias by conducting a sensitivity analysis using data for the subset of patients registered on the Trauma and Audit Network Database where complete data following discharge is available.

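### The missing-data sensitivity analysis varies the imputation method but names no departure from missing at random, the assumption the plan itself says cannot be proved

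*Protocol article*

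**What the plan says.** The Missing data section expects the problem: "As data are to be extracted from clinical records, missing variable data will inevitably occur". It accepts that the mechanism cannot be settled from the data: "it is generally impossible to prove that data are indeed MAR or whether they are not missing at random (MNAR". Imputation then proceeds "under a missing random assumption, so as to avoid excluding patients from the analysis", "with the exact method determined by the amount, type and distribution of the missing data". The one check attached to this step is that "a sensitivity analysis will be undertaken to determine how the substantive results depend on the multiple imputation method employed".

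Two other sensitivity analyses are described. In the Sensitivity analysis section, "the prognostic model will be estimated solely for the time period 2014–2017 and compared to the model estimated for the whole time period". In Limitations, on events missed after discharge, "We will estimate the effect of this possible bias by conducting a sensitivity analysis using data for the subset of patients registered" in the national trauma registry. The first varies calendar time and the second varies outcome capture. Neither changes the assumption about unrecorded predictors.

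**The concern.** The paragraph doubts one thing and tests another. Imputation methods that all assume missing at random can agree closely and share the same error.

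The doubt is a realistic one here. Table 1 lists vomiting, amnesia, seizures and signs of skull fracture among the candidate factors, all taken from retrospective notes. A clinician may well write down vomiting when it happened and write nothing when it did not. If that silence is coded missing, imputation under missing at random gives the symptom to some patients who never had it. Most of these did not deteriorate, but those who did are given it more often, because imputation conditions on the outcome. The risk estimated for patients left as symptom-free then falls. The Aims state that the model is meant to find patients who could be discharged from the ED, so an error in this direction would favour discharge.

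**Working it through.** **Inputs.** The protocol gives no figure for missing data, so there is none of its own to reproduce on this point. Its one relevant anchor is the 10% prevalence of deterioration (Sample size). Symptom prevalence, odds ratio and recording probabilities below are assumptions.

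**One symptom, large-sample calculation.** Assume prevalence 15%, odds ratio 3 and risk 8.0% if absent.

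- Odds if absent: 0.08/0.92 = 0.0870. Odds if present: 3 × 0.0870 = 0.2609, so risk if present is 20.7%.
- Overall risk: 0.85 × 0.080 + 0.15 × 0.2069 = 9.9%, in line with the protocol's 10%.
- Symptom prevalence in patients who deteriorate: 0.0310/0.0990 = 31.3%. In those who do not: 0.1190/0.9010 = 13.2%.

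Let r1 and r0 be the probabilities that the item is recorded when the symptom is present and absent. Imputation under missing at random, with the outcome in the imputation model, gives unrecorded patients the distribution seen in recorded ones:

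P(X=1 | Y, recorded) = r1·p / [r1·p + r0·(1 − p)], where p = P(X=1 | Y).

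Example with r1 = 0.95, r0 = 0.60:

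- Deteriorated: 0.2977/(0.2977 + 0.4120) = 41.9%. Not deteriorated: 0.1254/(0.1254 + 0.5208) = 19.4%.
- Imputed prevalence: 0.0990 × 0.419 + 0.9010 × 0.194 = 21.6%.
- Risk if symptom-free: 0.0990 × 0.5805/0.7836 = 7.3%, against a true 8.0%.

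| r1 / r0 | Missing | Imputed prevalence (true 15%) | Symptom-free risk (true 8.0%) |
|---|---|---|---|
| 95% / 80% | 18% | 17% | 7.8% |
| 95% / 60% | 35% | 22% | 7.3% |
| 95% / 40% | 52% | 29% | 6.7% |
| 60% / 95% | 0.15 × 0.40 + 0.85 × 0.05 = 10% | 10% | 8.55% |

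If r1 = r0 the formula returns p and there is no bias. The odds of having the symptom are multiplied by r1/r0 in both outcome groups, so the odds ratio stays at 3.0 in every row. Comparing coefficients would not show the error.

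**Wider range.** With overall risk 10%, prevalence 10% to 30%, odds ratio 2 to 5, and recording of 95%/60% or 95%/40%, symptom-free risk is understated by about 0.3 to 1.6 percentage points.

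**Would changing the method reveal it?** A simulation of 200,000 patients used three symptoms (each 20% prevalence, odds ratio 3, recorded 95% if present and 50% if absent). True risk with none of the three was 4.3%.

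| Imputation | Symptom-free risk |
|---|---|
| Missing at random, logistic | 2.73% |
| Missing at random, hot-deck | 2.70% |
| Missing at random, linear | 2.67% |
| Delta −1 on the log-odds scale | 3.34% |
| Delta −2 | 4.01% |
| Delta matching the assumed mechanism | 4.35% |

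Switching method moves the result by 2.73 − 2.67 = 0.06 points, against a bias of about 4.3 − 2.7 = 1.6 points. Varying the assumption reveals it.

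**Recoding unrecorded as absent.** In the 15% example with r1 = 0.95, symptom-free risk becomes (0.068 + 0.05 × 0.0310)/(0.85 + 0.05 × 0.15) = 8.1%, whatever r0 is. With 60% recording in both groups it becomes (0.068 + 0.40 × 0.0310)/(0.85 + 0.40 × 0.15) = 8.84%, where imputation under missing at random is unbiased. Recoding is therefore a bound and not a replacement.

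**The case against.** Several objections carry weight.

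- *A reader might infer that the planned imputation does understate risk.* The protocol does not support that. The result needs unmentioned symptoms to be coded missing and recorded more often when present. Data extraction does not say how silence in the notes is coded, and such a rule may sit in an extraction manual that is not shown. If silence is coded absent, these items are not imputed and this particular bias does not arise.
- *A reader might infer that blood tests, if taken less often in well patients, are not missing at random.* That does not follow. Table 1 includes GCS, blood pressure, oxygen saturation, age, comorbidity, frailty and CT severity. If these explain who was tested, the results are missing at random given them. A departure is possible but not established.
- *The illustrated group is not the discharge group.* An 8% risk is far from the 1/100 discussed under Model accuracy. At a true symptom-free risk of 1.0%, the same formula gives 0.97% (95%/80%) and 0.91% (95%/60%). The absolute shift is small, although the relative shift (9% at 95%/60%) is close to that in the 8.0% example (0.66/8.0 = 8%). No effect on sensitivity or specificity has been computed.
- *The wording leaves room.* The imputation method is left open, recognised guidelines are cited, and nothing forbids a method that departs from missing at random. That is so, but nothing commits to one either, and the only assumption named is missing at random.
- *Detail belongs in the analysis plan.* Delta values do. The purpose of the sensitivity analysis, however, is fixed in the article, and as stated it is not to test the assumption that the same paragraph questions.

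**Conclusion.** The point holds in conditional form. As written, the missing-data sensitivity analysis does not commit to varying the missing-at-random assumption, and no other named analysis does so. Agreement between imputation methods would therefore give no reassurance about it.

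The size and direction of any bias are unknown. Under the assumed recording pattern, symptom-free risk is understated by 0.2 to 1.3 points from 8.0% for one symptom, and by about 1.6 points from 4.3% for three. The larger one-symptom shifts need 35% to 52% of values missing. That the direction is unknown is itself a reason to test the assumption. This is a worthwhile and cheap improvement, not a flaw that invalidates the planned model.

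**What to change.** Keep multiple imputation under missing at random as the main analysis. State how a symptom not mentioned in the notes is coded. Pre-specify two departures as bounding checks:

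1. Symptom and sign items recoded as absent when not recorded.
2. Delta-adjusted imputation over a stated range, for symptom items (log-odds scale) and for blood and physiological values (SD units). The range should cover both directions.

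For a symptom item, the delta implied by given recording probabilities is ln[(1 − r1)/r1] − ln[(1 − r0)/r0]. Recording of 95%/80% gives −2.94 + 1.39 = −1.56, and 95%/40% gives −2.94 − 0.41 = −3.35. Clinicians can therefore choose the range by judging how often an item is written down.

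For each check, report the change in predicted risk and in sensitivity and specificity at the chosen cut-off, not only in coefficients.

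The cost is a few extra re-fits on data already held, a slightly longer results section and possibly a wider reported range for sensitivity. Design, sample size and data collection do not change.

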#### Model accuracy

The sensitivity and specificity of the model for detecting patients at low risk of deterioration will be calculated comparing the classification of each patient by the model with whether they actually deteriorated. To assess how informative lack of deterioration is, the model will be derived again for those patients who do not deteriorate within 24 h. We will determine whether a more accurate model can be produced for those still in hospital after 24 h.

A receiver operating characteristic (ROC) curve for both models will be plotted and the trade-off between the sensitivity and specificity of the model explored [30]. As indicated previously, a 1/100 risk of deterioration following discharge may be clinically acceptable, and therefore, our model will aim for at least a 99% sensitivity to deterioration [21].

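### Comparing the accuracy of a model re-derived at 24 h with the whole-cohort model does not show how informative 24 h without deterioration is; residual risk does

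*Protocol article*

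**What the plan says.** The Model accuracy section sets a question and a method in one sentence: "To assess how informative lack of deterioration is, the model will be derived again for those patients who do not deteriorate within 24 h". The criterion follows: "We will determine whether a more accurate model can be produced for those still in hospital after 24 h". So does the display: "A receiver operating characteristic (ROC) curve for both models will be plotted", after which the trade-off between sensitivity and specificity is to be explored. The same section restates the 1/100 risk that may be acceptable after discharge.

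The section does not say that the whole-cohort model will be evaluated in the 24 h patients, or that risk after 24 h will be set beside initial risk.

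The Model development section plans bootstrap validation and a shrinkage factor for the developed model, with one averaged estimate of optimism for the C-statistic. It does not say that this covers the 24 h model, or the ROC, sensitivity and specificity results.

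The sample size rests on the whole cohort: "We have based our sample size on a 10% estimated prevalence of clinical deterioration". No number or share of events after 24 h is given.

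**The concern.** What a day without deterioration tells a clinician is how far risk has fallen: from the risk at arrival to the risk that remains. A ROC curve or C-statistic describes how well a model ranks patients within a given group. If every patient's risk fell by the same proportion, ranking would hardly change, and the planned comparison would show no gain. If the patients who deteriorate early are mostly those at highest predicted risk, removing their events narrows the spread of risk and lowers the C-statistic. The comparison would then look like a loss, although stability had lowered risk.

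A second effect is that the 24 h set must contain fewer events than the whole cohort, for the same candidate factors. Apparent performance is therefore more optimistic there, so uncorrected curves can favour the re-derived model.

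At stake is a statement about whether a better discharge decision can be made after a day of observation. This is not one of the two listed aims, but it bears on the same decision.

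**Working it through.** **1. The plan's own figures.** Inputs from Sample size: "we will aim for 99% sensitivity for clinical deterioration", 10% prevalence, and a margin of 1.4%.
- Events needed = 1.96² × 0.99 × 0.01 / 0.014² ≈ 194. N = 194 / 0.10 = 1,940, which agrees with about 2000.
- Prevalence margin = 1.96 × √(0.10 × 0.90 / 2000) = 1.3%, as stated under Outcome estimate.
- Whole-cohort events = 2000 × 0.10 = 200. At 10 events per parameter this gives the stated 20 variables.

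All of these rest on about 200 whole-cohort events.

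**2. Residual risk at 24 h.** The early share is not in the article, so a range is assumed. Late events = 200 × (1 − early share). Patients event-free at 24 h = 2000 − early events. Intervals are exact binomial. The patients-at-risk figure ignores discharge before 24 h.

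| Early share (assumed) | Late events / patients | Residual risk (95% CI) | Late events per Table 1 row (32 rows) |
|---|---|---|---|
| 0% (initial risk) | 200 / 2000 | 10.0% (8.7 to 11.4) | 6.25 |
| 20% | 160 / 1960 | 8.2% (7.0 to 9.5) | 5.0 |
| 40% | 120 / 1920 | 6.3% (5.2 to 7.4) | 3.75 |
| 60% | 80 / 1880 | 4.3% (3.4 to 5.3) | 2.5 |
| 75% | 50 / 1850 | 2.7% (2.0 to 3.5) | 1.6 |
| 80% | 40 / 1840 | 2.2% (1.6 to 2.9) | 1.25 |

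The 32 rows are 13 + 14 + 5 from the three columns of Table 1; coding the categorical factors adds parameters. The direct answer is estimated with useful precision at every split shown, and can be read against 1/100.

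**3. Does the C-statistic track the fall in risk?** Simulation with 200 runs per scenario: 2000 patients, 10% prevalence, 32 independent normal candidates of which 8 are prognostic, and backward elimination at 0.05. The nominal late share was 40% or 20%. Where early events were tied to high risk, the late events averaged 102 and 62.

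| Scenario | Risk after 24 h | True C, whole cohort | True C, 24 h set |
|---|---|---|---|
| Timing unrelated to predictors, about 80 late events | 4.2% | 0.767 | 0.761 |
| Timing unrelated to predictors, about 40 late events | 2.2% | 0.766 | 0.767 |
| Early events in high-risk patients, about 102 late events | 5.3% | 0.768 | 0.678 |
| Early events in high-risk patients, about 62 late events | 3.4% | 0.764 | 0.629 |

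These are true values, free of overfitting. Risk falls in all four rows; C stays still in two and drops in two. Correcting for optimism cannot change this.

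**4. Fitted models.** In the first two scenarios the re-derived model had the higher mean apparent C (0.785 against 0.777; 0.788 against 0.774) and looked better in 62.5% and 64.5% of runs. In new data each model, tested in its own risk set, showed the reverse: 0.733 against 0.756, and 0.706 against 0.756. Optimism was 0.051 and 0.081 for the re-derived model, against about 0.02 for the whole-cohort model.

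**5. Same patients, both models.** In new event-free 24 h patients, the mean C of the whole-cohort model against the re-derived model was 0.751 against 0.733, 0.757 against 0.706, 0.669 against 0.631, and 0.623 against 0.555. Here the same factors drive early and late events by construction. If late deterioration has different predictors, the re-derived model could do better. Only a comparison in the same patients would show which applies.

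**The case against.** The strongest reply is that the design is a legitimate landmark analysis. The 24 h patients are a nested subset of the cohort, and re-deriving a model in them suits the aim of a usable model for those still in hospital. Its predicted probabilities are themselves residual risks, and the overall residual risk is a simple count in that set. All of this stands, so the model can stay. But the article names accuracy, not residual risk, as what answers the question.

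Second, a reader might infer that the comparison simply measures overfitting. The article does not support that. It plans a bootstrap and a shrinkage factor, and deriving the model again can fairly be read as repeating the whole procedure. What remains is that the text does not say so, and names only the C-statistic for the averaged optimism estimate. The simulated gap in apparent C is also small (0.008 and 0.014). The case-mix problem does not depend on any of this.

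Third, a reader might infer that the two event counts differ greatly, or that the 99% target means no missed events in the 24 h set. Neither is shown. Fewer events is certain, but the split is not given; at 20% early the counts are 160 and 200. The article aims for at least 99% sensitivity and explores the trade-off, without fixing an operating point for comparing the models.

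Fourth, the article says the curves will be plotted, not that one will be tested against the other, and a metric could be left to an analysis plan. That is fair for the metric. It does not help the stated criterion, because no accuracy metric computed separately in each risk set measures the fall in risk.

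**Conclusion.** The point holds in this form: the stated method does not answer the stated question. Discrimination in the whole cohort and in those event-free at 24 h can agree while risk more than halves (10% to 4.2%, C 0.767 and 0.761), or diverge through case mix while risk also falls (10% to 5.3%, C 0.768 and 0.678). This part follows from what the C-statistic measures and needs no assumption about the event split.

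Greater optimism in the 24 h model is a secondary point. Its direction follows from fewer events for the same candidates, but its size depends on the unknown split, on the simulated coefficients and independent predictors, and on whether the planned bootstrap covers both models. The simulated values show direction, not what this study will find.

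This is a worthwhile, inexpensive improvement to a secondary analysis. It does not affect the prevalence estimate or the derivation of the main model.

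**What to change.** 1. Answer the question of how informative 24 h of stability is by the residual risk of deterioration after 24 h, overall and within predicted-risk groups of the whole-cohort model, with exact confidence intervals, beside the initial risk and the 1/100 standard.
2. Keep the re-derived landmark model. Judge whether it is more accurate by applying it and the whole-cohort model, with its intercept re-estimated, to the same patients event-free at 24 h.
3. Repeat the planned bootstrap for both models in that comparison, and say that it covers the sensitivity and specificity results as well as the C-statistic.
4. State that no gain will be inferred from ROC curves drawn in the two different cohorts.

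Cost: analysis wording and a little code. No new data are needed, because event timing is already required to form the 24 h set. The 24 h model may look less favourable than on its own plotted curve.

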**Fig. 1 Fig1:**
[figure not shown]
Current management of minor head injured patients

The management of GCS13–15 patients with CT-identified TBI is controversial with some advocating admission to higher levels of care and mandatory repeat CT imaging due to the risk of deterioration [7]. Others argue that some patients are at low enough risk to be discharged safely from the ED after a short period of observation, a model of care adopted in a level 1 trauma centre in Arizona [8]. The UK NICE guidelines (published 2004, 2007 and 2014) state that all patients with significant brain injuries identified by CT imaging should be admitted to hospital, but do not qualify what constitutes such injuries [1].

In our recent systematic review, we estimated a pooled risk of neurosurgery in GCS13–15 patients with injuries identified by CT imaging of 3.5% (95% C.I. 2.2–4.9%) from the results of 36 studies [9]. A risk of clinical deterioration, such that patients would benefit from inpatient hospital admission, of 11.7% (95% C.I 11.7–15.8%) was derived from 18 studies. There was significant variation in estimates of these outcomes across individual studies, and no studies were conducted in the UK where NICE guidelines are used, so relevant risk factors were not considered. Following the introduction of the NICE guidelines, hospital admissions for head injury increased in England [10]. It is thought this may be due to more injuries of less clinical significance being identified due to increased CT imaging of minor head injured patients [10]. Research is required to estimate the risks of adverse outcomes in GCS13–15 patients with injuries identified by CT imaging in the UK.

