### Aims

Estimate the prevalence of clinical deterioration in initial GCS13–15 adult patients with brain injuries identified by CT imaging.Develop a multivariable model that accurately identifies adult patients at sufficiently low risk of clinical deterioration that they could be discharged from the ED.

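### A 99% sensitivity target does not by itself secure the 1/100 post-discharge risk from which the plan derives it

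*Protocol article*

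**What the plan says.** The second aim is a model that "accurately identifies adult patients at sufficiently low risk of clinical deterioration that they could be discharged from the ED".

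The Sample size section takes its tolerance from research on chest-pain discharge, where "a 1/100 risk of a patient being discharged who subsequently had a significant cardiac event may be an acceptable risk threshold" for patients and clinicians. It continues: "Therefore, we will aim for 99% sensitivity for clinical deterioration as this may correspond to a clinically acceptable level of model accuracy". The study size follows from that target: "A sample size of approximately 2000 patients is required, based upon the desired 99% sensitivity", so that "the maximum marginal error of the estimate does not exceed 1.4% with a 95% confidence interval". The prevalence used is 10% ("We have based our sample size on a 10% estimated prevalence of clinical deterioration in our systematic review").

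The Model accuracy section repeats the step: "a 1/100 risk of deterioration following discharge may be clinically acceptable, and therefore, our model will aim for at least a 99% sensitivity".

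The planned performance measures are the C-statistic, the Hosmer–Lemeshow test, sensitivity, specificity and the ROC curve. Specificity is to be made as high as possible, with no value stated. The article plans no estimate of risk among patients classed as low risk and sets no cut-off on predicted risk.

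**The concern.** A risk following discharge is conditional on having been discharged. Sensitivity is conditional on having deteriorated. The plan moves from one to the other with the word *therefore*, as if 1 in 100 on the first scale meant 99 in 100 on the second. No such identity exists: the link runs through prevalence and specificity.

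This matters because the second aim is about patients at sufficiently low risk, and 1/100 is the only yardstick the plan offers for that. If the model is judged on 99% sensitivity instead, the conclusion can be wrong in either direction. A model may be called adequate although its low-risk group exceeds 1/100, or inadequate although its low-risk group satisfies it.

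**Working it through.** **Inputs from the protocol article.** Prevalence p = 10%, target sensitivity Se = 99%, margin 1.4% at 95% confidence and N about 2000 (Sample size); acceptable post-discharge risk 1/100 (Model accuracy). As an alternative prevalence, the Background gives a pooled risk of deterioration "of 11.7% (95% C.I 11.7–15.8%) was derived from 18 studies". Specificity Sp is not given, so a range is assumed.

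**1. The plan's own figure.** Events needed = 1.96² × Se(1 − Se)/d² = 1.96² × 0.99 × 0.01/0.014² = 194. Dividing by 0.10 gives N = 1940, or 1950 if events are rounded up to 195. This agrees with approximately 2000. The arithmetic for estimating a 99% sensitivity is sound; what is in question is where the 99% comes from.

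**2. Post-discharge risk at 99% sensitivity.**

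Risk = 1 − NPV = (1 − Se)p / [(1 − Se)p + Sp(1 − p)]

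With 2000 patients there are 200 events and 1800 non-events. At 99% sensitivity 2 events are missed, so the risk is 2/(2 + 1800 × Sp).

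**3. Sensitivity that gives exactly 1/100.**

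Se = 1 − (0.01/0.99) × [(1 − p)/p] × Sp. At Sp = 50%: 1 − (0.01/0.99) × 9 × 0.50 = 95.5%.

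| Assumed specificity | Classed low risk, of 2000 | Risk at 99% sensitivity | Sensitivity giving 1/100 |
|---|---|---|---|
| 5% | 92 | 2/92 = 2.2% | 99.55% |
| 11% | 200 | 2/200 = 1.0% | 99.0% |
| 20% | 362 | 2/362 = 0.55% | 98.2% |
| 30% | 542 | 2/542 = 0.37% | 97.3% |
| 50% | 902 | 2/902 = 0.22% | 95.5% |

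**4. Where the two criteria coincide.** Setting the risk to 0.01 with Se = 0.99 gives Sp = 0.99p/(1 − p). At p = 10% this is 0.099/0.9 = 11.0%. At p = 11.7% it is 13.1%, and at p = 15.8% (the upper limit of the pooled estimate) 18.6%. The model refitted for patients without deterioration in the first 24 h would have a different prevalence; at an assumed 5% the two coincide at 5.2%. The same 99% therefore stands for a different risk in each setting.

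**5. Which side of 11% is plausible.** The article gives no expected discrimination. Under an assumed equal-variance binormal ROC at p = 10%, the 99%-sensitivity cut-off gives:

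| C-statistic | Specificity | Post-discharge risk |
|---|---|---|
| 0.70 | 5.7% | 1.93% |
| 0.75 | 8.5% | 1.29% |
| 0.80 | 12.8% | 0.86% |
| 0.85 | 19.5% | 0.57% |
| 0.90 | 30.4% | 0.36% |

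The crossing lies at a C-statistic of about 0.78, so either direction is possible.

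**6. Effect of the planned precision.** At the lower end of the margin, sensitivity is 99% − 1.4% = 97.6%. The specificity needed to keep the risk at 1/100 is then 0.024 × 0.10 × 99/0.90 = 26.4%.

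**The case against.** Several points on the other side have force.

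- **The limit may well be met.** At 10% prevalence and 99% sensitivity, post-discharge risk is at or below 1/100 at every specificity of 11% or more. Above that point the target is stricter than the plan's tolerance, which costs efficiency rather than safety. This stands.
- **99% is an aim, not a fixed cut-off.** The trade-off between sensitivity and specificity is to be explored, and the Sample size section says only that 99% may correspond to acceptable accuracy. This also stands. But the Model accuracy section states the inference without that hedge, and exploring a ROC curve cannot repair it, because the curve carries no information on prevalence.
- **The chest-pain threshold might be a miss rate.** The Sample size wording could loosely be read that way, and 99% sensitivity would then be its natural counterpart. The source cannot be checked here. The Model accuracy section, however, calls the 1/100 a risk following discharge.
- **1 minus NPV can be derived.** Prevalence, sensitivity and specificity will all be estimated in the same consecutive cohort. True, and a condensed article need not list every table entry. The fault is the stated inference, not the missing entry.
- **Replacing the target is a trade-off.** A criterion on 1 minus NPV alone could accept 95.5% sensitivity, about 9 missed events in 200 instead of 2. Whether that is acceptable is a clinical judgement, and the sample size was justified on precision for sensitivity. This stands, and it is why the fix does not require the sensitivity target to be abandoned.
- **The study only derives a model.** External validation and prospective testing are planned before any use. That limits the immediate harm, but this criterion still decides what the study concludes on its second aim.

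**Conclusion.** The inference from a 1/100 post-discharge risk to 99% sensitivity is wrong as written, in both the Sample size and Model accuracy sections. At the plan's 10% prevalence the two coincide only at a specificity of 11%. Over assumed specificities of 5% to 50%, 99% sensitivity corresponds to a post-discharge risk of 2.2% down to 0.22%.

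A reader might infer that the 99% target will breach the 1/100 limit. The documents do not support that: they state neither an expected specificity nor an expected C-statistic, and from 11% specificity upwards the limit is met. The supported conclusion is that 99% sensitivity neither guarantees the stated risk nor is always needed to reach it. Nor does the point touch the sample-size arithmetic, which reproduces.

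The algebra rests only on the plan's prevalence and target sensitivity. The specificities, the 5% prevalence and the binormal ROC shape are assumptions.

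**What to change.** 1. In the Sample size and Model accuracy sections, delete the inference that an acceptable 1/100 risk implies 99% sensitivity.
2. At each candidate cut-off, including the one giving 99% sensitivity, report the optimism-corrected risk in the low-risk group (1 minus NPV), its exact 95% upper limit and the proportion of patients classed as low risk, with sensitivity and specificity alongside.
3. Judge sufficiently low risk on that scale against the plan's own 1/100, for both the main model and the 24 h model.
4. If 99% sensitivity is kept as a target and as the basis of the sample size, justify it separately.

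**Cost.** Revised wording and a little more analysis; no new data. The plan's 1.4% margin concerns sensitivity only, and the interval for 1 minus NPV may be wide: 2 events among 200 low-risk patients is 1.0%, with an exact 95% upper limit of 3.6%. The study may therefore be unable to show with confidence that the risk is below 1/100, and the plan should say so.
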